## Secondary endpoints

- 30 day all-cause mortality
- 30 day cardio-vascular mortality
- Hospital readmission at 30 days
- Length of in hospital stay truncated at 30 days
- Changes of more than 2 fold in creatinine level from inclusionto day 30 or to discharge whichever comes first.

Creatinine will be measured at day 0 in the ED, and at discharge day or day30, whichever comes first.

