### D0 : inclusion and baseline visit

The inclusion visit takes place at day 0, during the ED index visit. Patients should be included during the first 6 hours after ED entrance.

As this is a cluster study, and the intervention consists of an application of recommended guidelines, all patients with AHF will be treated as per the care bundle according to the strategy period, whether in the study or not but their data will not be collected if patients are not included.

1. Inclusion

After having checked inclusion and exclusion criteria, the investigator will seek consent of participation.

-if the patient is able to provide his/her written informed consent : the investigator will inform the patient and obtain his/her written informed consent (for the utilization of his hospital data and 30 days follow-up).

- if the patient is unable to provide his written informed consent : the investigator will inform and obtain the consent of the trustworthy person, family member or close relative, as appropriate (Article L1122-2 of the French Public Health Code).

- if the patient is unable to provide his written informed consent and in the absence of the trustworthy person, next of kin or close relative : a procedure for inclusion in the study in emergency situation will be applied (article L1122-1-2 of the French Public Health Code). In this case, continuation-of-care consent for the study will be signed by the patient (if need be by trustworthy person, family member or close relative) as soon as possible, according to French Law (article L1122-1-2 of the French Public Health Code).

2. Baseline data

The local investigator will also collect with the help of clinical research technician the following variables at the time of the ED stay:

- Past medical history (Chronic heart failure, acute coronary syndrome, Chronic respiratory failure )
- Chronic oral intake of diuretics, nitrates, antibiotic, antiplatelet, anticoagulant.
- Baseline characteristics: heart rate, systolic and diastolic blood pressure, temperature
- ECG rhythm and signs of ischemia
- Main biological parameters if performed: haemoglobin, White blood cell count, troponin, BNP or nt-proBNP, creatinine, CRP, procalcitonin, arterial blood gas
- Treatment given in the ED in the first 4 hours:
  - Diuretics (dose and class)
  - Nitrates (dose and class)
  - Antibiotics
  - Antiplatelet or anticoagulant
  - Anti-arythmic (digoxine, cordarone)
  - Anticoagulant / LMWH
  - NIV

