### Follow-up visits (if discharge before 30 days)

If the patient is discharged before 30 days, the last value of creatinine measurement before discharge will be collected.

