## Principal criterion analysis

The number of days alive and out of hospital will be calculated based on date of admission, vital status, date of death and date of discharge will be collected. A death during follow-up will correspond to 0. An ED visit will correspond to “one day” at the hospital.

The number of days alive and out of hospital will be analysed using a linear regression mixed model with a random effect for each cluster, considered fixed effects will be: strategy and, for the stepped wedge design, time representing each step. In case of non-normality distribution of the interest variable, a transformation could be realized.

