## Secondary evaluation criteria

In hospital mortality, all causes mortality at 30 days and cardiovascular mortality at 30 days will be compared between groups by using Pearson's chi-square test or Fisher exact test.

If possible, generalized linear regression mixed model with Poisson distribution will be performed. If the number of events is sufficient, generalized linear regression mixed model using logit link will be performed.

The length of stay in hospital in days will be compared between the two periods by using Student t-test or Wilcoxon rank-sum test as needed. If possible, a linear regression mixed model will be performed. A random effect for each cluster will be considered and considered fixed effects will be: strategy and, for the stepped wedge design, time representing each step. In case of non-normality distribution of the interest variable, a transformation could be realized.

Percentage of patients with a change of more than 2 fold in creatinine between inclusion and 30 days will be compared between groups by using Pearson's chi-square test or Fisher exact test. If possible, generalized linear regression mixed model with Poisson distribution will be performed. If the number of events is sufficient, generalized linear regression mixed model using logit link will be performed.

Second analysis will be performed on the per protocol population.

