## Calculation hypotheses for the number of subjects required and the result

From our previous cohort, the mean number of days alive and out of hospital at 30 days was 14±9. To be clinically relevant, we estimate that the new approach should increase this endpoint of 3 days at least (a relative increase of 20%). With a power of 80% and alpha=5%, we need to include 283 patients. Since this study is planned as a stepped wedge cluster and after specification of following elements: 15 clusters, ICC=0.0001, the design effect is estimated at 1.609, so we need to analyze454patients – to take into account 10% of non-evaluable patients, it is necessary to include 500 patients -around 2 per cluster for each 2 weeks period.

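### The only renal endpoint is a yes/no cut at a 2-fold creatinine change; an analysis of the same two values on their full scale should be added beside it

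*Protocol*

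**What the plan says.** Section 4.2 of the protocol lists one renal item: "Changes of more than 2 fold in creatinine level from inclusionto day 30 or to discharge whichever comes first". It adds the sampling rule: "Creatinine will be measured at day 0 in the ED, and at discharge day or day30, whichever comes first". For patients discharged before day 30, section 6.1 says that "the last value of creatinine measurement before discharge will be collected". The baseline list in the same section is conditional: "Main biological parameters if performed: haemoglobin, White blood cell count, troponin, BNP or nt-proBNP, creatinine, CRP" and others.

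Section 13.3 gives the analysis: "Percentage of patients with a change of more than 2 fold in creatinine between inclusion and 30 days will be compared between groups", by Pearson chi-square or Fisher exact test. A Poisson mixed model follows if possible, and then: "If the number of events is sufficient, generalized linear regression mixed model using logit link will be performed".

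Other numeric outcomes stay on their scale. Days alive and out of hospital (section 13.2) goes into a "linear regression mixed model with a random effect for each cluster, considered fixed effects will be: strategy and, for the stepped wedge design, time", with a transformation allowed for non-normality. Section 13.3 offers the same model for length of stay. No counterpart is stated for creatinine. The protocol gives no expected rate of 2-fold change, no creatinine SD and no reason for the threshold.

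**The concern.** A threshold analysis uses only which side of the line each patient falls on. If the bundle moves creatinine modestly in most patients, few of them cross a distant line because of it, and the comparison of percentages can miss a shift that the paired values would show.

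This matters because it is the only planned renal comparison in a trial of intravenous furosemide and nitrates in patients aged 75 and over. A finding of no difference in 2-fold changes could be read as no renal effect, although it would say little about a moderate shift in either direction.

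The model terms matter too. Intervention patients are enrolled later on average in a stepped wedge. If the mixed models for the binary outcome prove infeasible, what remains is a chi-square or Fisher test with no centre or step term. A linear mixed model needs no minimum number of events and keeps both.

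**Working it through.** **1. The plan's own sample size (section 13.4).** Inputs: "the mean number of days alive and out of hospital at 30 days was 14±9", a gain of 3 days, 80% power, 5% level (two-sided reproduces the figure), 15 clusters, ICC 0.0001, design effect 1.609.

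- Unadjusted total: 4 × [9 × (1.960 + 0.842) / 3]² = 282.6; plan 283.
- With the design effect: 282.6 × 1.609 = 454.6; plan 454.
- With the 10% allowance: 454 × 1.10 = 499.4; plan 500.

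The figures reproduce, but they concern the primary endpoint only. Effective size per group: 454 / 1.609 / 2 = 141. Applying it to creatinine assumes equal groups, a complete pair of values for all 454 patients, and the same design effect for both analyses.

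**2. Power under a general shift (assumed).** Let log(follow-up / day-0 creatinine) be normal with mean 0 in control, mean d under intervention and common SD s. Shifts of 0.10 and 0.15 are ratios of about 1.11 and 1.16. Only rises are counted.

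- Cut: p0 = 1 − Φ(ln 2 / s) and p1 = 1 − Φ((ln 2 − d) / s), then two-sided 5% power for two proportions.
- Full scale: power = Φ(d / (s√(2/141)) − 1.96).

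Example with s = 0.35 and d = 0.10:
- p0 = 1 − Φ(1.980) = 2.4% and p1 = 1 − Φ(1.695) = 4.5%.
- Events = 227 × (0.0238 + 0.0451), about 16.
- Power of the cut is 16%.
- Full scale: 0.10 / (0.35 × 0.119) = 2.40, and Φ(2.40 − 1.96) = 67%.

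| SD | Shift | Over 2-fold, control / intervention | Events in 454 | Power, cut | Power, log ratio |
|---|---|---|---|---|---|
| 0.25 | 0.10 | 0.3% / 0.9% | 3 | 10% | 92% |
| 0.25 | 0.15 | 0.3% / 1.5% | 4 | 19% | 99.9% |
| 0.35 | 0.10 | 2.4% / 4.5% | 16 | 16% | 67% |
| 0.35 | 0.15 | 2.4% / 6.0% | 19 | 33% | 95% |
| 0.45 | 0.10 | 6.2% / 9.4% | 35 | 17% | 46% |
| 0.45 | 0.15 | 6.2% / 11.4% | 40 | 34% | 80% |
| 0.55 | 0.10 | 10.4% / 14.0% | 55 | 15% | 33% |
| 0.55 | 0.15 | 10.4% / 16.2% | 60 | 30% | 63% |

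The normal approximation for the cut is rough where only a handful of events are expected.

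**3. A second route, by event rate.** Under a normal shift, a cut crossed by a share p of controls keeps about φ(z)² / [p(1 − p)] of the information. Take the shift that the full scale detects with 80% power.

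| Control event rate | Information kept | Power of the cut |
|---|---|---|
| 1% | 7% | 14% |
| 2% | 12% | 19% |
| 5% | 22% | 31% |
| 10% | 34% | 42% |
| 20% | 49% | 53% |

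Simulated Fisher power is lower: 10%, 23% and 36% at rates of 2%, 5% and 10%.

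**4. The opposite case.** Suppose 5 to 8% of one group has about a 2.5-fold rise and everyone else is unchanged. In simulation, with 141 per group and SD 0.25 to 0.30, a t-test on the log ratio has 21 to 52% power and Fisher on the cut 45 to 93%. The ranking reverses.

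**5. Direction.** The text says change without saying whether a halving counts. If it does, a general shift adds events in one tail and removes them from the other, and on the grid in step 2 the power of the cut falls to about 4 to 12%.

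**The case against.** The strongest reply is that a 2-fold change is a readable threshold, that no secondary endpoint was powered, and that the power figures rest on a uniform shift which the protocol neither predicts nor calls important. All of that stands, as does the reversal in step 4. It rules out replacing the cut or reducing it to description; it does not argue against a second analysis beside it. A supplementary analysis might also sit in a statistical analysis plan that is not shown. But section 13.3 sets out a full method for this endpoint, and every part of it is binary.

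Four stronger readings are tempting, and the documents do not support them.

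- **That few events are expected.** No rate is given. The condition on a sufficient number of events is worded identically for mortality, which the protocol puts at around 10%, so it is not a forecast about creatinine.
- **That few events leave only chi-square or Fisher.** A Poisson mixed model is also named, if possible.
- **That renal harm would otherwise go unreported.** Section 10 sends adverse events to the applicable vigilance procedure instead of the sponsor.
- **That a complete pair exists for everyone.** Baseline biology is recorded only if performed. Patients sent home from the emergency department, or who die, may have no usable second value. This limits both analyses, since the cut needs the same two numbers.

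A further objection applies to the full-scale analysis itself. The second sample is taken at discharge or day 30, and the sponsor expects shorter stays under the intervention. A difference in mean creatinine could therefore partly reflect earlier sampling. That stands and has to be stated with the result.

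**Conclusion.** The point holds as a cheap improvement, not as an error in the plan. The protocol reduces two numeric creatinine values to one threshold and plans no full-scale analysis, although a suitable model is already specified. Under the assumed general shifts the cut has about 10 to 34% power against about 33 to 99.9% for the log ratio.

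This should not be read as a claim that the cut loses most of its power whatever happens. At a 20% event rate it keeps about half the information, and for large rises in a small subset it is the better test. The figures depend on the assumed SDs and shifts, normality of the log ratio, only rises counting, 454 complete pairs, and a design effect borrowed from the primary endpoint.

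**What to change.** In section 13.3:

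- Keep the 2-fold comparison as a tested endpoint.
- Add a prespecified analysis of log follow-up creatinine (discharge or day 30, whichever comes first), adjusted for log day-0 creatinine. Use the linear mixed model of section 13.2: random centre effect, fixed strategy and step.
- Report the exponentiated strategy effect as a geometric mean ratio with 95% CI, among patients with both values.
- Report by period the number of patients without both values.
- State that sampling time follows length of stay, which the intervention may change, and interpret the ratio with that in mind.

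Cost: a change of wording and one more model fit, with no new samples, visits or patients. If the change counts as substantial, section 15.9 requires sponsor and CPP approval. It should be settled before outcome data are seen. The downsides are one more secondary analysis, a summary measure less familiar to clinicians than a percentage, and low sensitivity to rare large rises, which is why the cut stays.

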## Calculation hypotheses for the number of subjects required and the result

From our previous cohort, the mean number of days alive and out of hospital at 30 days was 14±9. To be clinically relevant, we estimate that the new approach should increase this endpoint of 3 days at least (a relative increase of 20%). With a power of 80% and alpha=5%, we need to include 283 patients. Since this study is planned as a stepped wedge cluster and after specification of following elements: 15 clusters, ICC=0.0001, the design effect is estimated at 1.609, so we need to analyze454patients – to take into account 10% of non-evaluable patients, it is necessary to include 500 patients -around 2 per cluster for each 2 weeks period.

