# Research methodology

## Design of the study

The ELISABETH trial is designed as a stepped wedge cluster randomized trial. We decided to choose this design for the following reasons:

- As we implement a new protocol, there is a risk of contamination. An emergency physician, who would have already treated patients via the care bundle protocol, would be subsequently influenced by this trial, and could have difficulty to provide the former “standard of care”. Therefore, a randomization at the patient level or a cross-over design would induce bias through contamination. This bias was likely a reason why the recent “Guide It” trial failed to provide significant difference between control group and intervention group.^39^
- The present ELISABETH trial focus on a severe condition, in EDs that are often busy places, therefore the need for a randomization at the patient level could be an impediment to inclusion, and therefore limit our ability to recruit consecutive patients
- A cluster stepped-wedge design prevents contamination as centers will first be allocated to standard care, before implementing the intervention. Furthermore, a stepped wedge design would also prevent a potential “period effect” that could have resulted from a simple cluster before/after design

All the 15 participating centers will begin with a “control period” for 4 weeks. Then, every 2 weeks, one center will be randomized to switch to the “intervention period”. After 32 weeks, all centers will then be in the intervention group for a last 4-week period.

| **Weeks** | **1-2** | **3-4** | **5-6** | **7-8** | **9-10** | **11-12** | **13-14** | **…** | **27-28** | **29-30** | **31-32** | **33-34** | **35-36** |
| --- | --- | --- | --- | --- | --- | --- | --- | --- | --- | --- | --- | --- | --- |
| Center 1 | C | C | I+T | I | I | I | I | … | I | I | I | I | I |
| Center 2 | C | C | C | I+T | I | I | I | … | I | I | I | I | I |
| Center 3 | C | C | C | C | I+T | I | I | … | I | I | I | I | I |
| Center 4 | C | C | C | C | C | I+T | I | … | I | I | I | I | I |
| Center 5 | C | C | C | C | C | C | I+T | … | I | I | I | I | I |
| Center 6 | C | C | C | C | C | C | C | … | I | I | I | I | I |
| Center 7 | C | C | C | C | C | C | C | … | I | I | I | I | I |
| Center 8 | C | C | C | C | C | C | C | … | I | I | I | I | I |
| Center 9 | C | C | C | C | C | C | C | … | I | I | I | I | I |
| Center 10 | C | C | C | C | C | C | C | … | I | I | I | I | I |

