## Anticipated level of statistical significance

All tests will be performed at 5%.

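### Section 13.4's design effect of 1.609 fits a 32-week wedge; on the planned 36-week layout it is about 1.81, so 454 evaluable patients give about 75% power, not 80%

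*Protocol*

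**What the plan says.** Protocol section 13.4 starts from a previous cohort in which "the mean number of days alive and out of hospital at 30 days was 14±9" and takes a gain of 3 days as clinically relevant. Before any allowance for the design it states: "With a power of 80% and alpha=5%, we need to include 283 patients". It then inflates for the stepped wedge: "15 clusters, ICC=0.0001, the design effect is estimated at 1.609, so we need to analyze454patients". An allowance of 10% for non-evaluable patients brings the total to 500. The section does not say which design-effect formula was used, how many periods it assumed, or where the ICC comes from.

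The layout is fixed elsewhere in the protocol:

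- Section 5.1 and Figure 1: all centres are in control for weeks 1-4. One centre switches each fortnight, from weeks 5-6 (centre 1) to weeks 33-34 (centre 15). The section adds: "After 32 weeks, all centers will then be in the intervention group for a last 4-week period".
- Section 6.2 repeats this and gives 36 weeks of recruitment.
- Section 7.4 asks centres to recruit across the whole inclusion period.
- Section 13.2 analyses the primary endpoint with a linear mixed model: random centre effect, fixed effects for strategy and for time by step.

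**The concern.** A stepped-wedge design effect depends on the number of periods and on how many of them have every centre in the same condition. When time is a fixed effect and the ICC is close to zero, a fortnight in which all centres are in control, or all in intervention, contributes almost nothing to the strategy effect. Patients recruited then count towards the 454 but hardly towards the precision.

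Figure 1 has four such fortnights out of 18. If 1.609 was computed for a wedge with only two, the stated 80% power belongs to a different layout from the one the trial will run. That power is what the sample size of 500 rests on, and the trial would be less able to show a 3-day gain than its protocol says.

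**Working it through.** **Inputs.** From section 13.4: SD 9, difference 3, 15 clusters, ICC ρ = 0.0001, 80% power, 454 evaluable. Alpha is 5%; sidedness is not stated, but two-sided reproduces the 283. The model is that of section 13.2 and the layout that of Figure 1. One assumption is added: equal recruitment in every centre-fortnight.

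**1. Unadjusted size.** N = 4 × (1.96 + 0.8416)² × 9² / 3² = 282.6, that is 283. This matches the protocol.

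**2. The stated design effect.** The standard formula, with k steps, b baseline periods, t periods per step and n patients per cell, is

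DE = (b + kt) × [1 + ρ(ktn + bn − 1)] / [1 + ρ(ktn/2 + bn − 1)] × 3(1 − ρ) / [2t(k − 1/k)].

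With k = 15, b = 1, t = 1, n = 2:

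DE = 16 × (1.0031 / 1.0016) × 2.9997 / 29.867 = 16 × 0.10059 = 1.609.

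Then 282.6 × 1.609 = 454.6, against the stated 454. So the protocol's figure is reproduced with 16 fortnights: one all-control, 14 mixed, one all-intervention. With two baseline fortnights (b = 2) the formula gives 1.710. Other layouts tried also miss 1.609: for example, k = 16 with b = 1 gives 1.602, and k = 14 with b = 2 gives 1.725.

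**3. The layout in Figure 1.** Weeks 1-4 are two all-control fortnights, weeks 5-32 are 14 mixed fortnights, and weeks 33-36 are two all-intervention fortnights. That makes 18 fortnights and 15 × 18 = 270 cells, 135 in each condition. The generalised least squares variance of the strategy effect (random centre, fixed fortnight) was computed for each layout. The relations are SE = 2 × 9 × √(DE/454), power = Φ(3/SE − 1.96), and detectable difference = 2.80 × SE.

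| Layout, ICC 0.0001, 454 evaluable | DE | SE | Power | Difference detectable with 80% power |
|---|---|---|---|---|
| 16 fortnights | 1.609 | 1.072 | 79.9% | 3.00 days |
| 18 fortnights (Figure 1) | 1.810 | 1.137 | 75.2% | 3.18 days |

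The increase is what the reasoning predicts: at ICC zero the design effect goes from 1.607 to 1.808, which is 1.607 × 18/16. Coding time as 16 steps, with the first and last lasting four weeks, gives the same 1.810 and 75.2%.

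**4. Size needed for 80% on Figure 1.** 282.6 × 1.810 = 511.5, so 512 evaluable patients.

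**5. Sensitivity to the ICC (a separate matter).** The protocol gives only 0.0001. The other values below are assumptions.

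| Assumed ICC | Power, 16 fortnights, 454 | Power, 18 fortnights, 454 |
|---|---|---|
| 0.01 | 75.7% | 71.3% |
| 0.02 | 72.7% | 68.7% |
| 0.05 | 67.9% | 64.7% |

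**The case against.** **The origin of 1.609 is a reconstruction.** This stands: the protocol names no formula, and the match should be described as an inference. The result does not depend on it, because step 3 works directly from Figure 1 and gives 1.81 whatever the source of 1.609.

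**The primary analysis set is all 500, not 454.** Section 13.9 defines the ITT population as all included patients, and section 13.7 scores a missing primary outcome as 0 days. With 500 analysed on Figure 1, power is 79.1%, but only if nobody is missing. If the planned 10% are scored 0 in both periods, the difference shrinks to 0.9 × 3 = 2.7 days. Taking a mean of 15.5 (midway between 14 and 17), the SD becomes √(0.9 × 81 + 0.9 × 0.1 × 15.5²) = 9.7. Power is then about 64%. The imputation rule does not rescue the stated 80%.

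**The shortfall is moderate.** This also stands. It is about 5 percentage points at the protocol's own ICC. The endpoint, model and estimate are unaffected, and a null result will in any case be read from its confidence interval.

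Three stronger readings are tempting but not supported:

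- A reader might infer that the layout error brings power down to 65-71%. Those figures need ICCs that no document supplies. At the same ICCs the 16-fortnight layout also falls, to 75.7% at 0.01 and 67.9% at 0.05, so the layout accounts for only about 3 to 4 points there.
- A reader might take the closing words of the calculation, "it is necessary to include 500 patients -around 2 per cluster for each 2 weeks period", as proof of a 16-fortnight plan. They fit both layouts: 500/240 = 2.08 and 500/270 = 1.85 both round to 2.
- A reader might conclude that the trial should be cut to 32 weeks. Figure 1 has centre 15 in its training fortnight in weeks 33-34, so removing the last fortnight would leave that centre with intervention data from training only.

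**Conclusion.** The point holds. The design effect in section 13.4 does not describe the 36-week wedge fixed in sections 5.1 and 6.2. On that wedge it is about 1.81 instead of 1.609. Power for a 3-day difference with 454 evaluable patients is about 75% instead of 80%, and the difference detectable with 80% power is about 3.2 days instead of 3.0.

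These figures use the protocol's own SD, difference, ICC and model. They rest on a two-sided 5% test and on equal recruitment per centre-fortnight. That 1.609 came from a 16-fortnight calculation is an inference, though a close one. The sensitivity to the ICC is a second, independent weakness of the power statement: 0.0001 has no stated source, and larger values lower power in either layout.

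**What to change.** Recompute section 13.4 on the 36-week layout and state the number of periods and the cell size used. Report a design effect of about 1.81, power of about 75% with 454 evaluable patients, and a detectable difference of about 3.2 days at 80% power.

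In a separate sensitivity statement, give the source of the ICC or say that there is none, and show power on the 36-week layout for larger values labelled as assumptions: about 71% at 0.01, 69% at 0.02 and 65% at 0.05.

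This changes text only; layout, model and recruitment target stay as they are. The cost is a less favourable stated power.

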## Method for taking into account missing, unused or invalid data

Missing value for the principal criteria will be considered as failure (0 days alive and out of the hospital), whatever the period considered.

Sensitivity analyses will be performed to check the impact of replacement methods of missing values with missing data considered: 1) success (maximum days alive and out of the hospital observed in the total population of the study) in the experimental group and as failure (0 days alive and out of the hospital) in the control group; 2) failure in the experimental group and as success in the control group.

Others missing data will not be replaced.

- 1. Management of modifications made to the analysis plan for the initial strategy

Modification made in analysis will be documented in the final report.

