## Choice of individuals to include in the analyses

ITT population: all included patients according to the period assigned by the randomization to the center, regardless of the strategy effectively received by the patient.

Per protocol population: all included patients without major protocol deviation:

- No respect of selection criteria,
- No respect of strategy assigned by randomization (cross-over for example),
- Missing value for the principal criteria,
- Other major protocol deviation identified during data review and freezing of data base.

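### The 10% allowance in Section 13.4 is applied by multiplication and, more importantly, is not reconciled with an ITT analysis that keeps missing outcomes and scores them 0

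*Protocol*

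**What the plan says.** Section 13.4 builds the sample size in three steps.

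- From a previous cohort, "the mean number of days alive and out of hospital at 30 days was 14±9". With a target gain of 3 days, "With a power of 80% and alpha=5%, we need to include 283 patients".
- The stepped-wedge design is then allowed for: "15 clusters, ICC=0.0001, the design effect is estimated at 1.609", "so we need to analyze454patients".
- Finally, "to take into account 10% of non-evaluable patients, it is necessary to include 500 patients".

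The section defines neither the term non-evaluable nor the formula used for the allowance.

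Three other sections decide who is in the principal analysis. Section 13.1 makes it ITT. Section 13.9 defines that set: "ITT population: all included patients according to the period assigned by the randomization to the center". Section 13.7 deals with a missing primary outcome: "Missing value for the principal criteria will be considered as failure (0 days alive and out of the hospital), whatever the period considered". Section 13.9 also defines a per-protocol set, from which patients with a missing primary outcome are removed. Section 13.3 provides for a second analysis on that set.

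**The concern.** There are two separate questions about the same 10%.

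The first is arithmetic. To keep a target number after losing a fraction of patients, one divides by the fraction that remains. The protocol's figure matches multiplication by 1.10, which falls slightly short.

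The second matters more. An allowance for non-evaluable patients presumes that some included patients contribute nothing to the analysis. Under the ITT definition and the zero-scoring rule, a patient with a missing primary outcome stays in the principal analysis with a value of 0. Recruiting more patients makes up for lost ones. It does not make up for zeros, which pull both means towards 0, reduce the difference between periods and add variance. If the planned 10% are missing outcomes, the 80% power in Section 13.4 does not describe the analysis that the protocol specifies.

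**Working it through.** **Inputs, all from Section 13.4:** control mean 14, SD 9 (reading the ± as SD), difference 3 days, power 80%, alpha 5% (two-sided, which reproduces the stated figure), design effect 1.609 taken as stated, 454 to analyse, 10% allowance, 500 to include.

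**Step 1. Reproduce the protocol's figures.**
- Total N without clustering = 4 × [9 × (1.960 + 0.842)/3]² = 282.6; stated 283.
- With the design effect: 282.6 × 1.609 = 454.6; stated 454. (Starting from 283 gives 455.3.)
- Allowance: 454 × 1.10 = 499.4, rounded up to 500; stated 500.

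**Step 2. The allowance if 10% leave the analysis.**
- Number to include for 454 evaluable: 454/0.90 = 504.4, so 505 (506 if one starts from 455.3).
- Left from 500: 500 × 0.90 = 450, which is 4 short.
- Largest loss that 500 can absorb while keeping 454: 1 − 454/500 = 9.2%.
- Power = Φ(difference/SE − 1.96), with SE = 2 × SD/√(N/1.609).
 - N = 450: 450/1.609 = 279.7, SE = 1.076, power 79.6%.
 - N = 454: 454/1.609 = 282.2, SE = 1.072, power 79.9%.

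The slip costs about 0.35 percentage points.

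**Step 3. The allowance if the missing patients stay in and score 0.** All 500 are analysed, so 500/1.609 = 310.8. Let m be the proportion missing in each period.
- Difference = 3 × (1 − m).
- Variance = (1 − m) × 81 + m(1 − m) × 15.5², where 15.5 is the midpoint of the means 14 and 17.
- At m = 10%: difference 2.7; variance 72.9 + 21.6 = 94.5; SD 9.72; SE = 2 × 9.72/√310.8 = 1.103; power = Φ(2.448 − 1.960) = 68.7%. With the SD held at 9: SE = 1.021, power = Φ(2.644 − 1.960) = 75.3%.

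| Missing in both periods | Difference (days) | SD with zeros | Power, SD widened | Power, SD kept at 9 |
|---|---|---|---|---|
| 0% | 3.00 | 9.00 | 83.6% | 83.6% |
| 5% | 2.85 | 9.40 | 76.2% | 79.7% |
| 10% | 2.70 | 9.72 | 68.7% | 75.3% |

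The protocol gives no expected rate of missing primary outcomes. The rates in the table are therefore assumptions, with 10% chosen to match the allowance.

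**The case against.** **The arithmetic gap is trivial.** Five patients in 500 is 1%, and the protocol's other recruitment figures are coarser: 33 per site in 15 sites (Section 7.3) is 495. This stands. The slip deserves a correction in wording and does not make the trial underpowered.

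**The two problems cannot both occur.** If Sections 13.7 and 13.9 govern, a missing outcome removes nobody from the principal analysis, 500 are analysed and there is no shortfall to 450. If patients do leave, the dilution does not arise. This also stands, so the two losses must not be added together.

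**A reader might infer that Section 13.4 contradicts Section 13.7.** The text does not support that. Non-evaluable is undefined and need not mean a missing primary outcome. It could cover patients whose consent is refused after emergency inclusion (Sections 6.1 and 15.1), or per-protocol exclusions for eligibility failures or cross-over. Section 7.4 itself distinguishes patients included from patients who could be analysed. An allowance for such patients can coexist with zero-scoring among the rest. The per-protocol reading is less convincing, because the principal analysis is ITT and the per-protocol analysis comes second. A definition might also sit in the SAP, which was not available. Even so, the power that the protocol states needs one reading.

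**A reader might also infer that the trial has only 69% power.** That is the low end of a range that depends on assumptions. Follow-up is active: the patient, relatives and family practitioner are contacted, and the town hall is asked about deaths (Section 6.1). The missing rate may therefore be well under 10%. Deaths found this way score 0 by definition and are not extra dilution. It is also unknown whether the cohort's 14±9 already contains such zeros.

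**Conclusion.** The point holds, at modest size. On the protocol's own figures, 500 included with 10% excluded leaves 450, not 454, and 79.6% power; 454 evaluable would need 505. That part is rounding-level.

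The part that matters is that the allowance is not matched to the principal analysis. With missing outcomes scored 0 and all 500 analysed, power is about 84% with none missing, 76–80% with 5% missing and 69–75% with 10% missing. In each range the lower value widens the SD for the zeros and the upper value keeps it at 9. These figures assume design effect 1.609 as stated, equal missingness in both periods, missingness unrelated to outcome, and no such zeros already in the 14±9. The documents support an undefined term and an unstated power assumption. They do not establish a contradiction, a combined loss from both effects, or an actual power of 69%.

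**What to change.** Keep 500 and restate Section 13.4. Say which of two things non-evaluable means, and give the power that goes with it:

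- **Excluded from the analysis:** 450 evaluable, 79.6% power. Say on what grounds patients are excluded, given the ITT definition in Section 13.9.
- **Kept and scored 0 under Section 13.7:** 500 analysed, with the power range for a stated missing rate (76–80% at 5%, 69–75% at 10%) and the assumptions behind it.

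This is a change of wording in one section and needs no extra patients. The cost is a slightly less favourable stated power under exclusion, or a lower range under zero-scoring. If the sponsor prefers to guarantee 454 evaluable after 10% exclusions, the figure is 505, and the total in the summary and in the Section 7.3 table would then change as well.
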